## **5.2 Immunogenicity**

Serum samples will be obtained prior to vaccination, and 4 weeks post-vaccination. Moreover, serum samples of maternal subject at the end of gestation period (delivery) and the cord blood sample will also be obtained, if applicable. Serum samples will be tested for anti-hemagglutinin (HA) antibodies by hemagglutination inhibition (HAI), and assays will be performed at Adimmune Corporation designated central laboratory. Subjects will be considered to be seronegative if subjects' serum HAI titer  $< 1:10$ . The seroconversion is defined as the post-vaccination serum at least 1:40 for whom had negative pre-vaccination or a four-fold or greater increase in HAI titers in subjects who had positive pre-vaccination serum.

All antigens used in this study will be formalin-inactivated whole viruses. The testing

antigens will be provided by the designated laboratory. The standard microtiter method will be used. Antibody titrations will be done in duplicate and the titer assigned to each sample will be the geometric mean of two independent determinations.

### **5.3 Safety**

Safety data will consist of reactogenicity, serious and non-serious adverse events reported by the subject or observed by the investigator within 4 weeks after the vaccination, including 7 days after the dose of study vaccine. Vital signs will be performed at baseline and 4 weeks post-vaccination.

Reactogenicity events are pre-specified adverse events systematically recorded on diary cards (a grid of check boxes for each event and each day) during the immediate post-vaccination period by all participants. In general, reactogenicity events will be recorded for 7 days after vaccination. The selection of the events to be collected systematically is based on events expected to occur with wild-type influenza infection including fever ( $\geq 38^{\circ}\text{C}$ ), runny nose or nasal congestion, cough, sore throat, headache, muscle aches, vomiting, nausea and malaise. Furthermore, the local (injection site) reactions will also be evaluated that include soreness/pain, swelling, redness, ecchymosis and limitation of arm motion.

Adverse events of special interest, including influenza (with positive test for the presence of influenza), pneumonia (with positive X-ray or at least three of the six clinical criteria suggestive of pneumonia – reduced breathing frequency, dull percussion, local crepitation, bronchophony, temperature  $\geq 38^{\circ}\text{C}$  and thorax pain), heart failure (requires confirmation by cardiologist or at least three of five symptoms suggested of heart failure – edema, increased central venous pressure, pleural signs, enlarged heart, and dyspnea), stroke (diagnosed by a specialist), exacerbation of chronic pulmonary disease and other respiratory illness with fever, and all serious adverse events and adverse events of special interest on both maternal subjects and their infants will be monitored until 8 weeks after the delivery.

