### **5. STUDY PROCEDURES AND SCHEDULE**

#### **5.1 Study Procedure**

Each potential female subject will be screened before the start of the study to determine their eligibility for participation. The following examination will be performed and documented for each subject:

- Demographics including age, height, weight, weeks of gestation and influenza vaccination at 2010-2011 season;
- Blood pressure and heart rate and ear temperature;
- Review and record all medical history including history of allergy to food, medication or blood transfusion; concurrent and prior medical conditions; and immune system disorder and smoking history.
- Review and record all obstetric history, including but not limited to the first gestational age at birth, the gravidity (the number of times a woman has been pregnant), history of previous complicated pregnancy or preterm delivery, spontaneous or medical abortion, and congenital anomaly.
- Review and record all medication taken in the past month;

Just prior to vaccination, a 10 mL venous blood sample will be taken from each eligible subject, for baseline titration of circulating anti-HA antibodies. Immediately thereafter, each subject will receive one dose of vaccine (0.5 mL) by intramuscular injection into the upper arm. The injection should be given into the opposite arm which blood was drawn. Subjects will be asked to stay at the site for 30 minutes after the vaccination to observe for immediate

reaction.

Subjects will be monitored for all adverse events during the first 4 weeks. Each subject will be instructed to record symptoms once each day (evening) on a diary card for 7 days. The following symptoms will be recorded: fever ( $\geq 38^{\circ}\text{C}$ ), nasal congestion, cough, sore throat, muscle aches, headache, nausea, vomiting, malaise, eye redness, chest tightness, respiratory distress, and face edema. Moreover the local solicited adverse events, i.e., pain, swelling, redness, ecchymosis, and decrease limb mobility, at injection site will be recorded.

At 4 weeks after vaccination, subjects will be asked to return to the site for the second collection of blood samples. All adverse events during the first 4 weeks after the vaccination should be reported and recorded. The subject may return to the site according to her regular check-up schedule but the interval between the first and second blood sampling should be at least 3 weeks apart and no more than 5 weeks.

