## 6. ADVERSE EVENTS

All reported adverse events within 4 weeks after the vaccination will be recorded as much as possible. Adverse event during the 30-minute observation period after the vaccination will be collected on site. Reactogenicity within the first 7 days after the vaccination will be recorded in the diary card. Specific adverse events of interest, i.e., Guillain-Barre syndrome, anaphylaxis, convulsions, encephalomyelitis, central nervous system demyelinating diseases, Bell's palsy and vasculitis, will also be recorded in the CRF. Moreover, influenza, pneumonia, heart failure, stroke, exacerbation of chronic pulmonary disease and other respiratory illness with fever will also be recorded.

The term "adverse event" covers any sign, symptom, syndrome or illness that appears or worsens and is not of benefit to the subject during the period of observation in a clinical study. The term also covers laboratory findings (if applicable) or the results of other diagnostic procedures considered to be clinically relevant which:

- require additional diagnostic procedures not provided for in the study protocol
- require additional treatment measures not provided for in the protocol, or
- result in withdrawal of the subject from the study.

A study-emergent adverse event is defined as any event not present prior to signing informed consent or any event already present, which worsens in either intensity or frequency after signing informed consent. A treatment-emergent adverse event is defined as any event not present prior to exposure to study vaccine or any event already present, which worsens in either intensity or frequency following exposure to study vaccine.

The investigator is responsible for reporting all study-emergent serious adverse events and all treatment-emergent non-serious adverse events. If there is any doubt as to whether a clinical observation is a study or treatment-emergent adverse event, the event should be reported.

All adverse experiences must be rated on a 3-point scale of increasing severity, which defined as below:

Mild: Symptom barely noticeable to subject; does not influence performance or functioning. Prescription drug not ordinarily needed for relief of symptom but may be given because of personality of subject.

**Moderate:** Symptom of a sufficient severity to make subject uncomfortable; performance of daily activities influenced; subject is able to continue in study; treatment for symptom may be needed.

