**Severe:** Symptom causes severe discomfort. May be of such severity that subject cannot continue the study. Severity may cause cessation of treatment with test drug; treatment for symptom may be given and/or subject hospitalized.

**Baseline medical condition:** It is not necessary to complete an adverse event form for adverse medical conditions present at baseline, which do not worsen in either intensity or frequency during the study. These adverse conditions should be adequately documented in the case report form and any other appropriate ancillary documents. Adverse medical conditions present at baseline, which become worse following exposure to study vaccine, should have an adverse event record completed.

**Reactogenicity:** events are pre-specified adverse events systematically recorded on diary cards (a grid of check boxes for each event and each day) during the immediate post-vaccination period by all participants. In general, reactogenicity events will be recorded for 7 days. The selection of the events to be collected systematically is based on events expected to occur with wild-type influenza infection. The events include fever ( $\geq 38^{\circ}\text{C}$ ), runny nose or nasal congestion, cough, sore throat, muscle aches, headache, vomiting, nausea and malaise. Furthermore, the local (injection site) reactions will also be evaluated that include soreness/pain, swelling, redness, ecchymosis and limitation of arm motion.

**Serious adverse events:** An adverse event which meets one or more of the following criteria is considered serious and must be reported in an expedited fashion:

- Results in death
- Is life-threatening
- Requires subject hospitalization or prolongation of existing hospitalization
- Results in persistent or significant disability/incapacity
- Is a congenital anomaly/birth defect
- Is medically important

Subjects experience the following events during the gestation period will also be reported as an serious adverse events: Guillain-Barre syndrome, anaphylaxis, convulsions, encephalomyelitis, central nervous system demyelinating diseases, Bell's palsy, vasculitis,

influenza, pneumonia, heart failure, stroke, exacerbation of chronic pulmonary disease and other respiratory illness with fever.

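### The clinical definition of the special-interest event pneumonia in Section 5.3 counts a lowered breathing rate, which does not suggest pneumonia; the item should be checked against its source and corrected.

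*Protocol*

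**What the plan says.** Section 5.3 gives two alternative routes to the event: "pneumonia (with positive X-ray or at least three of the six clinical criteria suggestive of pneumonia". The six signs begin "reduced breathing frequency, dull percussion, local crepitation, bronchophony", and end with a temperature of at least 38°C and thorax pain.

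The same section extends follow-up to the children: "adverse events of special interest on both maternal subjects and their infants will be monitored until 8 weeks after the delivery". It gives no separate pneumonia definition for infants.

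Section 6 names pneumonia twice without any criteria. In its opening paragraph: "Moreover, influenza, pneumonia, heart failure, stroke, exacerbation of chronic pulmonary disease and other respiratory illness with fever will also be recorded". In the paragraph on serious adverse events, the conditions to be reported as serious when they occur during gestation again include "influenza, pneumonia, heart failure, stroke, exacerbation of chronic pulmonary disease and other respiratory illness with fever". Section 5.3 is therefore the only place in the protocol that says what counts as pneumonia.

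**The concern.** The list is offered as signs that suggest pneumonia. Five of the six do. The first does not: the expected change in breathing rate is upward. The likeliest explanation is a drafting or translation slip, but a site has no other text to work from.

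Read literally, the item errs in both directions. A woman breathing fast scores nothing on it, and a woman breathing slowly scores a point. Pneumonia is one of the few special-interest events with explicit diagnostic criteria, and during gestation it is also handled as a serious adverse event. A faulty sign can thus alter both the pneumonia count and the label under which a serious event is reported.

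A smaller question arises from the extension to infants. A newborn cannot report thorax pain, and bronchophony needs a speaking patient, so two of the six signs cannot be elicited.

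**Working it through.** The protocol states no figure on this point, so there is nothing to reproduce. The check is a reading of the rule, followed by an illustration of how far it could matter.

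**Reading the rule**

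1. Routes to the event (Section 5.3): positive X-ray, or at least 3 of 6 signs.
2. A patient with fast breathing cannot score the first sign. Her clinical route becomes 3 of the other 5.
3. The classification changes only when there is no positive X-ray and exactly two of the other five signs are present. With three or more of those five she qualifies anyway; with one or none she fails under either wording.
4. Conversely, slow breathing plus exactly two other signs qualifies, although the first of the three does not point to pneumonia.
5. The vital signs listed at screening in Section 5.1 are "Blood pressure and heart rate and ear temperature". Breathing rate is not among them, so that list would not supply the figure needed to reclassify a case later.

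**Illustration of the loss on the clinical route**

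Assumptions, none taken from the protocol:

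- The patient truly has pneumonia, with no positive X-ray.
- Each of the other five signs is present with probability *q*, independently.
- A correctly worded first item would be present with probability *t*, independently of the rest.
- Slow breathing does not occur in true cases.

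Formulae:

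- As written: P(at least 3 of 5) = Σ C(5,k) q^k (1−q)^(5−k), for k = 3, 4, 5.
- With the item corrected: the same, plus t × C(5,2) q² (1−q)³.
- Loss = t × 10 q² (1−q)³.

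Example with q = 0.5 and t = 0.6: as written 50.0%; exactly two of five = 10 × 0.25 × 0.125 = 31.25%; loss = 0.6 × 31.25 = 18.75 points; corrected 68.75%, or 68.8% rounded.

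| q | As written | Exactly 2 of 5 | Loss, t = 0.4 | Loss, t = 0.6 | Loss, t = 0.8 |
|---|---|---|---|---|---|
| 0.3 | 16.3% | 30.9% | 12.3 points | 18.5 points | 24.7 points |
| 0.4 | 31.7% | 34.6% | 13.8 points | 20.7 points | 27.6 points |
| 0.5 | 50.0% | 31.3% | 12.5 points | 18.8 points | 25.0 points |
| 0.6 | 68.3% | 23.0% | 9.2 points | 13.8 points | 18.4 points |
| 0.7 | 83.7% | 13.2% | 5.3 points | 7.9 points | 10.6 points |

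The loss runs from about 5 to 28 percentage points. The calculation does not depend on which corrected wording was intended: *t* is simply the chance that the intended sign is present.

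**Infants**

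Six signs less thorax pain and bronchophony leaves four. If the breathing item is not scored either, three remain (percussion, crepitation, temperature), and the rule becomes three of three.

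**The case against.** The strongest objection is that the protocol has several nets under this definition, and each of these stands:

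- A positive X-ray qualifies alone, and so do any three of the other five signs.
- The special-interest list also contains "exacerbation of chronic pulmonary disease and other respiratory illness with fever". A febrile case that fails the six-sign rule can be recorded there, is followed over the same period, and during gestation is reported as serious just as pneumonia is.
- A hospitalised or medically important case is a serious adverse event under any label.
- All adverse events are recorded for the first four weeks, whether or not they meet a definition.

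Outright loss therefore needs a narrow case: no fever, no positive X-ray, exactly two of the four remaining signs, not serious, and arising after week 4. A reader might infer that true pneumonias generally go unrecorded. The protocol does not support that; much of the harm is mislabelling.

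Other stronger readings are also tempting and do not hold:

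- **The error makes the vaccine look safer.** The item can admit false cases as well as exclude true ones, and the study is single-arm and descriptive, with no test on pneumonia. No net direction is shown. Avoidance of chest X-ray in pregnancy is not something the protocol states.
- **Half the definition is faulty.** Of the C(6,3) = 20 minimal three-sign combinations, C(5,2) = 10 include the breathing item. That counts subsets as if they were equally likely and says nothing about patients. Likewise 1/60 = 1.7 percentage points is only the weight of one woman among the 60 planned.
- **Breathing rate was certainly meant, with the direction reversed.** The neighbouring items are percussion and auscultation signs, so reduced breath sounds may have been intended. In that case it would be right to give fast breathing no credit.
- **Infants need a new rule based on physician diagnosis.** That would be a different event definition with no basis in the protocol. Infants keep the X-ray, serious-event and febrile-illness routes, and Section 2.3 counts neonatal complications separately.

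It is also fair to say that the protocol does not contradict itself here. The judgement that the sign is wrong rests on general clinical knowledge.

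**Conclusion.** The point holds in limited form. The first clinical sign for pneumonia in Section 5.3 does not suggest pneumonia, nothing elsewhere in the protocol corrects it, and a site following the text would misclassify cases that turn on it.

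The effect is confined to cases without a positive X-ray and with exactly two of the other five signs. The illustrative loss of about 5 to 28 points of clinical-route sensitivity rests on independent signs, *q* between 0.3 and 0.7, and *t* between 0.4 and 0.8. It shows that the item can matter; it does not estimate this trial's error. Many of the affected cases would still appear in the safety data under another heading.

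The pneumonia count and the classification of safety events are touched. The primary immunogenicity endpoint, the power statement and the sample size are not. Whether the six-sign list was meant for infants is left open by the text and should be confirmed, but the main point does not depend on it.

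**What to change.** 1. Check the first pneumonia sign in Section 5.3 against the definition from which the list was taken, and correct it. The intended wording may be increased breathing frequency or reduced breath sounds; the protocol does not settle which.
2. If the CRF repeats the item, make it match. The CRF is not available here, so whether it carries the same wording is unknown.
3. Confirm in the same edit whether the six-sign list is meant to apply to infants, given that two of its signs cannot be elicited in newborns.

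The cost is a one-line correction, a CRF check, and a sentence on infants. No visit, procedure or analysis is added.

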## 5.4 Schedule

The following table details the study schedule of procedures for study period:

|                              | Visit 1 |        |          | Visit 2               | Visit 3          | Follow-up              |
|------------------------------|---------|--------|----------|-----------------------|------------------|------------------------|
|                              | Week 0  | Week 1 | Week 2~3 | Week 4  | Delivery /Birth  | 8 Weeks after Delivery |
| Inform Consent               | X       |        |          |                       |                  |                        |
| Inclusion/Exclusion Criteria | X       |        |          |                       |                  |                        |
| Vital Signs                  | X       |        |          | X                     |                  |                        |
| Weight and Height            | X       |        |          |                       |                  |                        |
| Medical History              | X       |        |          |                       |                  |                        |
| Pregnancy History/Outcome    | X       |        |          |                       | X                |                        |
| Serum Samples                | X       |        |          | X                     | X  |                        |
| Dosing                       | X       |        |          |                       |                  |                        |
| Adverse Events               | X-----X |        |          |                       | X  | X        |
| Reactogenicity events        | X-----X |        |          |                       |                  |                        |
| Diary Card                   | X-----X |        |          |                       |                  |                        |
| Concomitant Medications      | X-----X |        |          |                       |                  |                        |

: The subject will return to the site for blood sampling according to her regular check-up schedule. However, the interval between the first and second blood sampling should be at least 3 weeks apart and no more than 5 weeks.

: Including maternal serum (within 8 weeks after delivery) and cord serum

: Serious adverse events and adverse events of special interest should be collected

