### **2.1 Primary Objective**

- To evaluate the immune response of the three vaccine viral strains by calculation of the geometric mean titers (GMT) of anti-HA antibodies, geometric means of post- to pre-vaccination antibody titer ratios, seroprotection rates, and seroconversion rates.

The primary endpoint will be the seroprotection rate which is defined as the proportion of subjects with HAI titer  $\geq 1:40$ . The other immunogenicity endpoints include seroconversion rate and geometric mean folds increase in HAI titer. Immunogenicity profile will be assessed before vaccination, 4 weeks after the vaccination and at the end of gestation period.

Moreover, the HAI titer of the cord blood will also be measured and compared with the maternal blood sample.

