### **3. STUDY DESIGN**

#### **3.1 Study Design**

This is a prospective, single-arm, descriptive clinical study to observed the safety and immunogenicity profile of the use of AdimFlu-S (2011-2012 season) vaccine in pregnant female subjects. All eligible participates will receive one dose of vaccine (0.5 mL) by intramuscular injection into the upper arm. Blood serum prepared from blood samples will be collected from each maternal subject immediately prior to vaccination and 4 weeks after vaccination; moreover, blood sample at the end of the gestation period (delivery) and the cord blood sample will also be collected, if applicable. Anti-hemagglutinin (HA) antibody titers will be determined using the WHO hemagglutination inhibition reference technique and the analysis will be observer-blinded. Safety outcomes included immediate reactions at the time of vaccination, solicited local and systemic reactions for 7 days, unsolicited adverse events until the first post-vaccination serum collected, and serious adverse events and adverse events of special interest until 8 weeks after the delivery.

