At the end of gestation period, blood samples from maternal subjects and from the cord blood will be collected, if applicable. Pregnancy outcome, including but not limited to the status of delivery, abortion and the date and/or the week of pregnancy of the event, will be recorded. The child information, including but not limited to the birth height and weight of the infant, sex of infant, Apgar score at 1 min and 5 min, and other information specified in the CRF, will be collected. All serious adverse events and adverse events of special interest will be followed until 8 weeks after the delivery.

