## 5.5 Serum Sample Randomization and Blinding

All serum samples sent to analysis laboratory will be under the blinded matter. On the serum samples used for antibody titrations there will be no information available regarding subject background data (e.g., age, pre- or post-serum). The serum will be re-labeled with serum number according to the randomization list for serum samples before being sent to the analysis laboratory. For each subject, there will be four randomization numbers allocated, one for the pre-vaccination serum sample (Visit 1), one for the post-vaccination serum sample (Visit 2, Week 4), one for the end of gestation period (Visit 3, delivery) serum sample from maternal subject (within 8 weeks after delivery) and one for the cord blood sample (Visit 3).

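### The maternal "delivery" serum may be drawn up to 8 weeks after birth, so it may not match the cord sample in time, and the end-of-gestation results may mix delivery and postpartum values

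*Protocol*

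**What the plan says.** Three sections tie the third maternal sample to delivery and to the cord blood:

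- Section 3.1: "blood sample at the end of the gestation period (delivery) and the cord blood sample will also be collected, if applicable".
- Section 5.1: "At the end of gestation period, blood samples from maternal subjects and from the cord blood will be collected, if applicable".
- Section 5.2: "serum samples of maternal subject at the end of gestation period (delivery) and the cord blood sample will also be obtained, if applicable".

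Two sections allow a later draw. In section 5.4 the serum mark for Visit 3 stands in the delivery/birth column, but its footnote (2) reads "Including maternal serum (within 8 weeks after delivery) and cord serum". Section 5.5 keeps the delivery label for the maternal Visit 3 serum and attaches the same 8-week limit; it gives the cord sample no such allowance. The separate follow-up column at 8 weeks after delivery has no serum mark.

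Section 2.1 gives the uses of the sample. It plans that "the HAI titer of the cord blood will also be measured and compared with the maternal blood sample", and it states: "Immunogenicity profile will be assessed before vaccination, 4 weeks after the vaccination and at the end of gestation period". Sections 2.3 and 7.4 carry the end of gestation forward as a reporting time for seroprotection and seroconversion; section 2.3 does so for the titer ratio as well.

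**The concern.** A cord titer is fixed at birth. If the maternal titer is read weeks later, part of any difference between the two reflects the date of the maternal draw and not the relation between mother and infant at birth. The delay may differ from woman to woman, so the distortion need not be a constant that could be removed afterwards.

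The same sample supplies the maternal end-of-gestation results. Under the present wording a serum taken 8 weeks postpartum counts as an end-of-gestation value. A fall in titer since delivery would lower those rates and ratios; an influenza infection after delivery could raise them.

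This is a matter for the protocol, because the collection window is fixed there. A statistical analysis plan can set late samples aside, but it cannot recover a maternal serum that was never drawn at birth.

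**Working it through.** The protocol states no figure on this point that could be reproduced. The check compares the stated times and then illustrates the size.

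**Timing**

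| Sample | Nominal time | Latest permitted draw |
|---|---|---|
| Maternal, Visit 2 | Week 4 | 5 weeks after the first sample (earliest 3 weeks) |
| Cord, Visit 3 | Delivery/birth | No window given |
| Maternal, Visit 3 | Delivery/birth | 8 weeks after delivery |

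Permitted gap between cord and maternal Visit 3 serum: 0 to 8 × 7 = 56 days. The Visit 2 window is 5 − 3 = 2 weeks wide; the Visit 3 window is 8 weeks wide.

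**Effect on the cord/maternal ratio, from decay alone**

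The half-life H of the maternal titer is an assumption, taken over 8 to 52 weeks. With exponential decay, a draw t weeks after birth multiplies the ratio by 2^(t/H). At the limit, t = 8. If draws were spread evenly over 0 to 8 weeks, the mean delay would be 4 weeks and the geometric mean ratio would change by 2^(4/H).

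| H (weeks) | Draw at 8 weeks | Draws spread evenly over 0 to 8 weeks |
|---|---|---|
| 8 | 2^1.000 = 2.00 | 2^0.500 = 1.41 |
| 12 | 2^0.667 = 1.59 | 2^0.333 = 1.26 |
| 26 | 2^0.308 = 1.24 | 2^0.154 = 1.11 |
| 52 | 2^0.154 = 1.11 | 2^0.077 = 1.05 |

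**Effect on end-of-gestation seroprotection, from decay alone**

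Further assumptions: true seroprotection at delivery is 80%, and log2 titers are normal with SD 1.5 to 2.3. If every woman were sampled at day 56, the measured rate would be Φ(0.842 − 56/(H × SD)), with H in days.

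| H (days) | SD 1.5 | SD 2.3 |
|---|---|---|
| 56 | Φ(0.842 − 0.667) = 56.9% | Φ(0.842 − 0.435) = 65.8% |
| 90 | Φ(0.842 − 0.415) = 66.5% | Φ(0.842 − 0.270) = 71.6% |
| 180 | Φ(0.842 − 0.207) = 73.7% | Φ(0.842 − 0.135) = 76.0% |
| 365 | Φ(0.842 − 0.102) = 77.0% | Φ(0.842 − 0.067) = 78.1% |

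With draws spread evenly over the 56 days, the 180-day row becomes 76.9% to 78.0%. These figures show scale only. They do not predict the trial's results, since neither the half-life nor the actual draw dates can be learned from the protocol.

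**The case against.** The strongest reply is that the 8 weeks are a tolerance around a nominal visit, as the 3 to 5 weeks are around week 4. Section 5.5 puts the delivery label and the window in one phrase, and section 5.1 collects both bloods together. On that reading most maternal samples would be drawn at birth. This stands in part: the window allows late draws and does not require them. A reader might infer that the two samples are in fact taken at different times, but the protocol does not show that. What remains is that a tolerance of 8 weeks on one member of a pair, and none on the other, undoes the pairing whenever it is used.

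A reader might also infer that the primary endpoint is compromised. The protocol does not support that. The primary endpoint is seroprotection, and its week 4 value is untouched. The cord comparison appears in section 2.1 after the endpoints; it is not among the outcome measures in section 2.3, and section 7.4 sets out no analysis of it. Which maternal sample is the comparator is itself an inference: the Visit 3 sample is the natural reading, but section 2.1 does not name it.

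Nor should the factor of 2.0 be read as the expected bias. It needs the shortest assumed half-life together with a draw at the limit. The net direction is not established either: decay raises the cord/maternal ratio, and postpartum infection could lower it. Recognized influenza can be identified, since section 5.3 follows test-positive cases until 8 weeks after delivery.

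Finally, time from vaccination to delivery already varies, because section 3.3.1 sets no upper limit on gestation at entry. That weakens the point for the maternal-only rates, where the window adds at most 8 weeks. It does not weaken it for the cord pair, where the gap between the two samples is what counts.

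**Conclusion.** The concern holds as a conflict in sampling time that can distort a result. The protocol describes one maternal sample as taken at delivery and also allows it up to 56 days later. The cord/maternal comparison is the more exposed of the two uses; the end-of-gestation seroprotection, seroconversion and titer ratios are exposed to a lesser degree.

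For a draw at the limit, decay alone would change the cord/maternal ratio by a factor of 2.0 to 1.11 under assumed half-lives of 8 to 52 weeks, and by 1.24 at 26 weeks. The effect is smaller if few draws are late and absent if none are. The conflict in the text is certain; the size and net direction of any bias are not. The change should be made because it is cheap and because a sample missed at birth cannot be replaced. The material does not support saying that the comparison is already biased.

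**What to change.** 1. Reconcile sections 5.4 (footnote 2) and 5.5 with sections 3.1, 5.1 and 5.2, so that the maternal Visit 3 serum is drawn during the delivery stay, alongside the cord blood.
2. In section 2.1, name that sample as the comparator for the cord titer.
3. Record the draw date of every Visit 3 maternal sample.
4. Base the main cord/maternal comparison on pairs drawn around birth. The protocol gives no basis for a particular cut-off in days, so the sponsor should choose one and justify it.
5. Keep all evaluable samples in the end-of-gestation endpoints, as the population in section 7.2 implies, and add a sensitivity analysis that excludes later postpartum draws or lists them separately. Removing them outright could lose a non-random share of the 60 women.

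The cost is wording in a few sections and one date field. The cord blood is already being taken at birth, so the maternal draw needs no extra visit. The downside is that some late samples leave the paired comparison; how many cannot be judged from the protocol.
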